## Abstract

**Introduction:**

Given the prevalence and staggering cost of neurological disorders, there is dire need for effective early detection and intervention tools. Emerging evidence suggests that multidisciplinary lifestyle interventions (MLI) may mitigate the risk and progression of neurological disorders. The objectives of this protocol are (1) to test the impact of MLI on the progression of neurological disorders and (2) to identify multi-omic biomarkers for early stages of neurological disease and the impact of MLIs on these biomarkers.

**Methods and analysis:**

We present the Multidisciplinary lifestyle Interventions for Neurological Disorders during the Silent phase (MINDS) protocol, a randomized controlled trial of MLI in neurologically healthy older adults (≥ 50 years old) exhibiting elevated risk for common neurological disorders: stroke, epilepsy, Parkinson’s Disease, or Alzheimer’s disease and related dementias. Participants will be randomly assigned to intervention (*n* = 100) or control (*n* = 100) groups. The intervention group will receive 3 months of weekly 2-hour sessions on diet education, yoga, music therapy, and cognitive skills training. The participants’ neurological health and engagement in relevant lifestyle practices will be assessed at regular intervals for 12 months. Neuroimaging and samples for multi-omic analyses will be collected at baseline, and at 3 months and 12 months after enrollment. Primary outcomes will be signs of progression of the neurological disorder risk that qualified them for study enrollment or a clinical diagnosis of the disorder. Secondary and exploratory outcomes will be based on self-reported health and multi-omic data. Data analysis will include between-group and longitudinal within-group analyses.

**Perspectives:**

The MINDS protocol and trial aims to clarify the impact of MLI on the progression of neurological disorder risk or diagnosis in older adults and to identify biomarkers that can be used to confirm MLI efficacy. The ability to validate the impact of MLI on neurological disorder progression based on biomarker data allows the identification of individuals most likely to benefit from such therapies in the early stages of neurological disease.

**Trial registration:**

The trial is registered on the National Institutes of Health (NIH) ClinicalTrials.gov (NCT05984056) site. It was registered on August 2nd, 2023. The trial has full approval of the Cleveland Clinic Internal Review Board.

**Supplementary Information:**

The online version contains supplementary material available at 10.1186/s42466-024-00334-3.

## Background

In 2017, approximately 12 million people in the United States had at least one of four major neurological disorders: Parkinson’s Disease (PD), Alzheimer’s disease and related dementias (ADRD), epilepsy, and stroke [1]. Globally, these neurological disorders of older adults were estimated to be responsible for over 8.5 million deaths and the loss of nearly 190 million disability-adjusted life years in 2019, with increases likely given the rapidly aging population and longer life spans [2]. 

The development of preventive measures and early intervention strategies to reduce this disease burden of neurological disorders is needed, as candidates for early intervention can be identified based on prodromal features, biomarkers, and clinical risk factors. Lifestyle interventions, such as yoga, music therapy, cognitive skill, dietary interventions, reductions in alcohol and tobacco use, and exercise, can impact the risk of development and progression of neurological disorders in older adults. These lifestyle interventions can alleviate the impact of PD symptoms on quality of life, have positive effects on behavioral, cognitive, and psychological symptoms in ADRD, impact cognitive decline in the pre-dementia stages, lower blood pressure, and prevent/treat hypertension [3–10]. Together, results indicate clear benefits of lifestyle interventions on neurological disorder progression. Evidence also demonstrates that multidisciplinary lifestyle intervention (MLI) has greater impact on neurological disorder progression compared to a single lifestyle change [11]. However, the mitigation of risk of development and progression of neurological disorders in older adults through MLI is challenged by the lack of reliable biomarkers that can predict the influence of MLI on preclinical indicators disease and the progression to disease state.

Here, we present the Multidisciplinary lifestyle Interventions for Neurological Disorders during the Silent phase (MINDS) study protocol for an open-label, randomized controlled trial to investigate the impact of MLI on neurological disorder progression in older adults exhibiting elevated risk of neurological disease, and to identify biomarkers that can be used to confirm MLI efficacy.

## Methods

### Aims of the trial

We aim to test the impact of MLI on neurological disorder progression in patients identified as at risk of stroke, epilepsy, PD, or ADRD associated with the a) transition from ‘at-risk’ preclinical (silent) stage to the worsening of clinicopathological changes or a diagnosis of a neurological disorder and b) the progression of pathological changes leading to the development of a neurological disorder. An additional goal of the MINDS study is to identify biomarkers that predict MLI’s efficacy in disease prevention or neuropathology progression in these patients.

### Study description and study design

This 12-month study is an open-label randomized controlled trial with parallel participant assignment into intervention and control arms (Fig. 1). The study will enroll individuals from the ongoing Cleveland Clinic Brain Study (CCBS), a longitudinal study of neurologically healthy adults (≥ 50 years old) at the Cleveland Clinic academic medical center, who are at-risk for transitioning to a neurological disorder [12]. A study team member who has been trained in the study protocol will provide the participant with information related to the study, obtain informed consent, and enroll the participant in the study if they choose to participate. CCBS participants undergo a thorough history and physical examination conducted by advanced practice providers with specialization in neurological care; a battery of surveys on quality of life, sleep, and mental health; neuropsychological testing [NP; includes the Brief Assessment of Cognitive Health (BACH), Tombaugh Trails test, Rey Auditory Verbal Learning Test (RAVLT), Boston Naming Test (BNT), Digit Span, Judgment of Line Orientation (JLO), and the Activities of Daily Living Questionnaire (ADLQ)]; brain magnetic resonance imaging (MRI); optical coherence tomography (OCT); and overnight electroencephalography (EEG) and polysomnography (PSG) along with biospecimen (blood, stool) collection for genomics, proteomics, and metabolomics analyses. Questionnaires include Perceived Stress Scale (PSS-10); Generalized Anxiety Disorder 7 Item (GAD-7); Patient Health Questionnaire Depression Scale (PHQ-8); Neuro-QoL (Quality of Life in Neurological Disorders) surveys for Sleep Disturbance, Ability to Participate in Social Roles and Activities, Lower Extremity Function, and Upper Extremity Function; PROMIS (Patient-Reported Outcomes Measurement Information System) Global Health, Healthy Aging Activity Engagement Scale, and General Self Efficacy Scale.This 12-month study is an open-label randomized controlled trial with parallel participant assignment into intervention and control arms (Fig. 1). The study will enroll individuals from the ongoing Cleveland Clinic Brain Study (CCBS), a longitudinal study of neurologically healthy adults (≥ 50 years old) at the Cleveland Clinic academic medical center, who are at-risk for transitioning to a neurological disorder [12]. A member of the study team who has been trained in the study protocol will provide the participant with information related to the study, obtain informed consent, and enroll the participant in the study if they choose to participate. CCBS participants undergo a thorough history and physical examination conducted by advanced practice providers with specialization in neurological care; a battery of surveys on quality of life, sleep, and mental health; neuropsychological testing [NP; includes the Brief Assessment of Cognitive Health (BACH), Tombaugh Trails test, Rey Auditory Verbal Learning Test (RAVLT), Boston Naming Test (BNT), Digit Span, Judgment of Line Orientation (JLO), and the Activities of Daily Living Questionnaire (ADLQ)]; brain magnetic resonance imaging (MRI); optical coherence tomography (OCT); and overnight electroencephalography (EEG) and polysomnography (PSG) along with biospecimen (blood, stool) collection for genomics, proteomics, and metabolomics analyses. Questionnaires include Perceived Stress Scale (PSS-10); Generalized Anxiety Disorder 7 Item (GAD-7); Patient Health Questionnaire Depression Scale (PHQ-8); Neuro-QoL (Quality of Life in Neurological Disorders) surveys for Sleep Disturbance, Ability to Participate in Social Roles and Activities, Lower Extremity Function, and Upper Extremity Function; PROMIS (Patient-Reported Outcomes Measurement Information System) Global Health, Healthy Aging Activity Engagement Scale, and General Self Efficacy Scale.

**Fig. 1 Fig1:**
[figure not shown]
Study Timeline. MINDS study timeline, including recruitment, randomization, and data collection, shown from participant selection through the final study visit CCBS = Cleveland Clinic Brain Study. MINDS = Multidisciplinary lifestyle Interventions for Neurological Disorders during the Silent phase

### Arms and interventions

Two hundred participants will be randomized equally to two study arms (*n* = 100 each): the intervention arm and the control observational arm. The sequence of group allocation was generated by the study data scientist using computer-generated random numbers and uploaded to the secure study REDCap database, where it can be administered by the study team. Each participant’s start date is based on participant availability, and, once enough participants (at least five) are identified that can meet at the same time, an intervention group and matching control group of comparable size will begin study activities on the same schedule. The experts completing quality assurance of the testing and analysis of the multi-omic data, including imaging, electrophysiology, and patient reported outcome measures are blinded to group allocation.

The intervention group will receive synchronous, virtual 2-hour weekly intervention sessions for 12 weeks. The control group will receive the standard of care during this time. Both groups will receive a MINDS study activity survey (see Supplemental Material 1) every 2 weeks during the first 12 weeks, followed by every month until the end of the 12-month study period. Each two-hour intervention session includes check-in and discussion of homework, followed by two 50-minute sessions, split evenly between two of the four intervention domains, with rotation through the domains and topics each week so that participants receive an even dose of intervention domain. See Supplemental Material 2 for an overview of the 12-week intervention sessions.

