#### Cognitive skills

This intervention teaches participants cognitive compensatory strategies and more general psychosocial strategies to optimize brain health. Brain health strategies include mental engagement, social engagement, exercise, and stress management. Cognitive compensatory strategies are intended to mediate and accommodate for any cognitive difficulties (such as impaired working memory). These strategies may increase functional independence, reduce the impact of cognitive changes related to aging, and delay the onset and progression of neurological disorders [16, 17]. Sessions include group counseling led by a licensed neuropsychologist.

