#### Sample size calculation

Our enrollment goal is 200 participants randomized to each group (intervention and control). Based on an attrition rate of 10%, we estimate we will have 180 participants with data for analysis. For primary outcomes analysis of binary outcomes (i.e., progression/no progression), the detection of a standard large effect size (odds ratio = 4.27, converted from Cohen’s *d* = 0.8) of the intervention at 0.8 power with a two-sided alpha of 0.05 would require 18% of the control group attaining progression. For secondary outcomes between group mixed-effects regression analysis, we will be able to detect a medium effect size (Cohen’s *f* = 0.27) at 0.8 power and a 5% significance level.

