#### Data analysis plan

We will use a modified intention-to-treat population approach and include participants with valid baseline data and at least one post-baseline data point. Missing data among these participants will be handled using multiple imputations, clearly described, and with sensitivity analysis to test the robustness of the results.

Primary outcome analysis will be completed using a Fisher’s exact test to compare the proportions of progression in the intervention and treatment groups. To analyze secondary and exploratory outcomes between groups, we will use mixed-effects regression models to evaluate change in outcome as a function of group, time, and group-by-time interaction. We will also conduct longitudinal analysis within groups using repeated measures ANOVA to compare measures at time points, with covariates as fixed effects. Effect sizes and confidence intervals will be reported. Additionally, we will assess baseline sample characteristics and test for any baseline group differences using two-sample t-tests for continuous variables and Chi-square tests for categorical variables. We will also conduct an adherence analysis by reporting intervention session attendance rate and summary statistics for self-reported engagement with intervention domains and testing for any differences in these adherence metrics based on cohort number, age/sex, and other covariates. We will conduct sensitivity analyses aligned with best practices to see if the outcome analysis results are robust to any potential confounders, including baseline imbalance or intervention non-compliance.

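### The intervention is given in live groups in one arm only, but no stated outcome analysis includes the delivery cohort; with a positive within-cohort correlation, the secondary and exploratory between-group models would understate their standard errors

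*Protocol article*

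**What the plan says.** **Delivery.** Under Arms and interventions, allocation is individual: "Two hundred participants will be randomized equally to two study arms", 100 in each. Participants start in batches: "once enough participants (at least five) are identified that can meet at the same time, an intervention group and matching control group" of similar size follow one schedule. "The intervention group will receive synchronous, virtual 2-hour weekly intervention sessions for 12 weeks", and each session opens with a check-in and a discussion of homework. Under Cognitive skills, "Sessions include group counseling led by a licensed neuropsychologist". For the other arm, "The control group will receive the standard of care during this time".

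**Analysis.** Under Data analysis plan, the primary binary outcome is compared by Fisher's exact test. Between-group secondary and exploratory outcomes use "mixed-effects regression models to evaluate change in outcome as a function of group, time, and group-by-time interaction". The further biomarker model adjusts for age, sex and education. Cohort appears once, in the adherence analysis, which includes "testing for any differences in these adherence metrics based on cohort number".

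**Power.** Under Sample size calculation: "Based on an attrition rate of 10%, we estimate we will have 180 participants with data for analysis". The section then gives 0.8 power for an odds ratio of 4.27 if 18% of controls progress, and a detectable Cohen's f of 0.27 for secondary outcomes. It states no intraclass correlation (ICC) and no design effect.

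**The concern.** Participants are randomised one by one, but those in the intervention arm are then treated together. Peers, session dynamics and, where they differ between cohorts, instructors can make outcomes within a group more alike than outcomes between groups. Controls have no such source of correlation. A model containing only arm, time and their interaction, with no term for the delivery group, counts each intervention participant as independent information. If the correlation is positive, p-values are then too small and confidence intervals too narrow.

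The secondary outcomes are the ones most exposed. They include self-reported stress, anxiety, depression, self-efficacy and social participation, on which a shared group experience could plausibly act. The Perspective section also leans on them: it says that the progression rate needed for the primary analysis may be hard to reach in 12 months, and that more sensitive secondary outcomes will support it.

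**Working it through.** **Inputs from the article.** 100 randomised per arm; 10% attrition, so 180 analysable, or 90 per arm; control progression 18%; odds ratio 4.27; two-sided alpha 0.05; a minimum of five people per batch.

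**Assumed, because the article does not give them.** Group size m of 5 to 10; within-cohort ICC ρ of 0.01 to 0.10; equal total outcome variance in the two arms. For a group-by-time effect, the relevant ρ is that of the change in outcome.

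**1. Reproduce the stated power.** Control odds are 0.18/0.82 = 0.2195. Dividing by 4.27 gives 0.0514, so intervention progression is 0.0514/1.0514 = 4.89%. The normal-approximation power for 18% against 4.89% with 90 independent participants per arm is 0.794, which matches the stated 0.80. The primary power figure therefore makes no allowance for clustering. (For Fisher's test itself, exact power at 90 per arm is 0.761.) The secondary figure of f = 0.27 cannot be traced in the same way: a simple two-group comparison of 180 participants reaches 0.80 power at f = 0.21, and the section does not say how 0.27 was obtained.

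**2. Effect on the between-group mixed models.** Clustering multiplies the variance of the intervention-arm mean by 1 + (m − 1)ρ and leaves the control arm unchanged. So:

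- variance ratio V = ([1 + (m − 1)ρ] + 1)/2
- true standard error relative to modelled = √V
- actual size of a nominal 5% test = 2[1 − Φ(1.96/√V)]

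For example, with m = 10 and ρ = 0.05, V = (1.45 + 1)/2 = 1.225, √V = 1.107 and 1.96/1.107 = 1.771, which gives 7.7%.

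| m | ρ | V | √V | Actual size |
|---|---|---|---|---|
| 5 | 0.01 | 1.02 | 1.01 | 5.2% |
| 5 | 0.05 | 1.10 | 1.05 | 6.2% |
| 5 | 0.10 | 1.20 | 1.10 | 7.4% |
| 10 | 0.01 | 1.045 | 1.02 | 5.5% |
| 10 | 0.05 | 1.225 | 1.11 | 7.7% |
| 10 | 0.10 | 1.45 | 1.20 | 10.4% |

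The effective intervention-arm sample falls from 90 to 90/1.04 ≈ 86 in the mildest row and to 90/1.90 ≈ 47 in the most severe.

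**3. Effect on the Fisher primary.** The sizes above are for a normal-approximation test, so Fisher's test was simulated separately: 90 per arm, 18% progression in both arms, beta-binomial clustering in the intervention arm only, 200,000 trials per setting. Without clustering its size is about 3.2%.

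| m | ρ = 0.01 | ρ = 0.05 | ρ = 0.10 |
|---|---|---|---|
| 5 | 3.4% | 4.1% | 5.0% |
| 10 | 3.6% | 5.2% | 7.5% |

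Only large groups combined with ρ = 0.10 take it materially above 5% (7.1% with groups of 9, 7.5% with groups of 10). Simulated Fisher power barely moves, from about 0.76 without clustering to 0.74 in the worst setting.

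**4. Direction of the calendar matching.** Each batch also pairs intervention and control participants in time. Variance common to both arms cancels in their difference, so ignoring it makes the standard error too large. With a shared component only, at ρ = 0.05, the size is 2[1 − Φ(1.96/√0.95)] = 4.4%.

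**The case against.** The strongest reply is that the article lists only the fixed terms of the mixed models and says nothing of their random effects. That structure is commonly left to an analysis plan, which is not at hand, so a cohort random effect is not ruled out. This stands, and the point must be put conditionally: the models as stated name no cohort term. It does not dispose of the point, because the article records cohort, thinks it worth testing for adherence, and names it in no outcome analysis.

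Four further limits stand.

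- The ICC is unknown. At 0.01 the effect is slight.
- Group size is uncertain. If the minimum of five counts both arms together, groups could be as small as 2 or 3. At ρ = 0.05, V is then 1.025 or 1.05 and the size is 5.3% or 5.6%.
- Not all contact time is clearly interactive. Group counselling is stated for one of the four domains, and nothing says that instructors differ between cohorts.
- A cohort term in the primary model would be poorly supported. About 0.0489 × 90 = 4.4 intervention-arm events are expected, spread over 18 groups of 5 or 9 groups of 10.

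A reader might infer that the primary test runs at 6% to 10%. It does not: those figures belong to a normal-approximation test, and Fisher's conservatism absorbs most of the effect. A reader might also take the unmodelled calendar matching as a second source of inflation. It acts the other way and costs precision.

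**Conclusion.** The point holds for the secondary and exploratory between-group comparisons, conditional on a positive within-cohort ICC. Across assumed ICCs of 0.01 to 0.10, a nominal 5% test runs at about 5.2% to 7.4% with groups of 5 and 5.5% to 10.4% with groups of 10. These are ranges under assumption and not estimates for this trial. The sizes use normal critical values, and the small number of cohorts is a further reason for a degrees-of-freedom correction.

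The primary analysis is largely safe: about 3% to 5% in most settings, and about 7% to 7.5% only with groups of 9 or 10 and an ICC of 0.10. That protection was calculated at 18% progression. The documents do not support the flat statement that standard errors are too small, nor any claim that the primary result would be unreliable. The plan should be changed because the cohort variable is already held and the remedy is cheap.

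**What to change.** 1. In the secondary and exploratory between-group mixed models, add a delivery-cohort random effect acting in the intervention arm only, with Satterthwaite or Kenward-Roger degrees of freedom. A calendar-cohort effect common to both arms is optional and would serve precision.
2. Keep Fisher's exact test for the primary outcome, and prespecify one sensitivity analysis that allows for cohort clustering, acknowledging that few events will limit it.
3. Under Sample size calculation, state that the power and detectable-effect figures assume independent participants, or restate them under an assumed ICC and cohort size. For a cluster-adjusted normal test of the primary outcome at ICC 0.05, power would be about 0.76 with groups of 5 and 0.72 with groups of 10, against 0.794 under independence.

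**Cost.** No new data are needed. At ICC 0.05, intervals for the affected comparisons are about 5% wider with groups of 5 and 11% wider with groups of 10, before the degrees-of-freedom correction. With roughly 9 to 18 cohorts, the cohort variance will itself be estimated imprecisely.

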#### Yoga

During instructor-led, gentle yoga sessions, the yoga intervention focuses on practicing breathing, meditation, and mindfulness. A recent meta-analysis indicates that yoga leads to improved cognitive function acutely (i.e., right after a session), as well as chronically [13]. Yoga sessions in the MINDS study are led by certified yoga therapists.

